##### Measurements

The above analyses of healing rate and time of complete re-epithelialisation will be made separately for each method of measurement. Photographs will be assessed blind to allocated treatment by two trained observers at the University of Birmingham (Fig. 2). Inter-rater reliability of the measurements will be made on 20% of ulcer photographs and assessed using interclass correlation coefficients.

Measurements are based on the ARANZ ® and tablet-based cameras (see Fig. 2). The ARANZ® images are measured in two ways: (1) manual tracings and (2) automatic tracings of wounds using a camera specifically designed to obtain standardised photographs of ulcers for scientific purposes. The distance of the camera from the ulcer surface is controlled by triangulation of three laser lights. The images taken by the camera in the tablet are calibrated digitally by reference to a measurement ruler in the frame. The areas (cm^2^) are then generated within the different software packages. We will measure, agreement between the methods of measurement:
The Push tool vs. the automated ARANZ® methodThe automated vs. manual ARANZ® method

#### Interim analyses {21b}

An interim analysis will be conducted when at least 49 participants have been followed-up for a minimum of 42 days. The rationale for this analysis is the detection of a ‘penicillin-like’ benefit or statistically significant negative effect of the treatment on either of the two main endpoints. A statistical threshold of 0.01, one-sided (0.02 two-sided) will be used for either of the two main endpoints. In the event that more than 10% of control participants cross-over from one arm to another at 42 days, we will consider performing a complier average causal effects analysis to the 70 day outcome.

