#### Sample size {14}

Sample size is based on the two primary outcomes: rate of healing and time to complete re-epithelialization. On the latter, we assume that 70% of ulcers will heal within 42 days with standard care [21]. Further, assuming that the intervention will increase this proportion to 90% and hazards are constant and proportional, for a two-sided test of the hazard ratio with a type I error of 5% and statistical power of 80% and a 1:1 allocation ratio, 47 individuals are required in each group. To allow for withdrawals and right censoring, we aim to recruit 65 patients in each group. We expect rate of healing to provide yet more precise estimates.

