### Analyses and inference

#### Statistical methods for main endpoints {20a}

##### Time to healing

Time to healing will be analysed using a Cox proportional hazards model with and without adjustment for baseline characteristics (trial ulcer area and participants’ age) allowing for right-censoring. For the rate of healing analysis, we will define the outcome as the ulcer size in cm^2^ at each time point and include in the model time since admission, treatment status and their interaction. Our parameter of interest will be that of the interaction term, which will be interpreted as the mean difference in rate of healing (in cm^2^ per unit time) between intervention and control groups. We will analyse this model using a linear mixed-effects model with participant-level random effects and both with and without adjustment for participant characteristics. Given there are multiple primary outcomes (two outcomes, with and without adjustment, for three types of ulcer assessment), we will adjust reported p values for multiple testing using a stepdown method, which provides an efficient means of controlling the family-wise error rate [25]. We will derive the approximate distributions of the test statistics to perform the stepdown procedure using a permutation test approach, by simulating 10,000 re-randomisations of the individuals [26].

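### The interim threshold (two-sided 0.02 on either main endpoint at 49 of 130 participants) is too lenient for its stated aim of detecting a 'penicillin-like' benefit, and inflates false positives if a crossing is acted on

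*Protocol article*

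**What the plan says.** All references are to the protocol article.

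- Interim analyses {21b}, timing: "An interim analysis will be conducted when at least 49 participants have been followed-up for a minimum of 42 days".
- Same section, purpose: "the detection of a ‘penicillin-like’ benefit or statistically significant negative effect of the treatment on either of the two main endpoints".
- Same section, rule: "A statistical threshold of 0.01, one-sided (0.02 two-sided) will be used for either of the two main endpoints". It states neither what follows a crossing nor whether the final significance level is reduced.
- Sample size {14} is worked out "for a two-sided test of the hazard ratio with a type I error of 5% and statistical power of 80% and a 1:1 allocation ratio", with nothing deducted for an interim look.
- Time to healing, under Statistical methods for main endpoints {20a}, adopts a stepdown procedure "which provides an efficient means of controlling the family-wise error rate". The tests it lists are two outcomes, with and without adjustment, for three types of ulcer assessment. The interim look is not listed.
- The Data Monitoring Committee section {21a} has the committee review efficacy and safety data and advise on continued recruitment.

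**The concern.** A look meant to pick up only an overwhelming benefit should be hard to cross when the effect is ordinary. This one uses |z| > 2.326 at about 38% of participants and may be crossed on either of two endpoints. Two things are at stake.

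- **Purpose.** If an effect of about the planned size is enough to cross, the rule does not separate a dramatic benefit from the one the trial was sized for. A crossing would also rest on 49 participants and would on average overstate the effect.
- **Error control.** The interim tests add chances of a false positive. Nothing in the article shows them being paid for, either in the stepdown family or in the 5% used for sample size.

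**Working it through.** **Inputs from the article.** Healing at 42 days: 70% control, 90% intervention, constant and proportional hazards; two-sided 5%, 80% power; 47 per group needed, 65 per group recruited (Sample size {14}). Interim at 49 participants, 0.02 two-sided per endpoint (Interim analyses {21b}).

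**Assumptions, because the article gives no figure.** Correlation between the two endpoints' test statistics: 0 to 0.9. Healing events among 49 participants: 0.70 × 49 = 34.3 to 0.80 × 49 = 39.2. The upper value uses the planned average healing proportion; the lower uses the control proportion throughout.

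**1. The plan's own figure reproduces.** HR = ln(0.1)/ln(0.3) = 1.912, log HR = 0.648. Events = 4(1.960 + 0.842)²/0.648² = 74.7. Divided by 0.80 this is 93.3 participants, or 47 per group, as stated.

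**2. Observed HR that crosses.** With d events, the standard error of log HR is about 2/√d, so the crossing value is exp(2 × z/√d).

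| Two-sided threshold | d = 39.2 | d = 34.3 |
|---|---|---|
| 0.02 (z = 2.326) | 2.10 | 2.21 |
| 0.001 (z = 3.291) | 2.86 | 3.08 |

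Against 70% healed in controls, HR 2.10 to 2.21 means 1 − 0.3^HR = 92 to 93% healed. The design value is 90%.

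**3. Chance of crossing under the planned effect, time to healing alone.** Mean z = 0.648 × √d/2 = 2.03 (d = 39.2) or 1.90 (d = 34.3).

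- At 0.02: P(z > 2.326) = 38% or 33%.
- At 0.001: P(z > 3.291) = 10% or 8%.
- Among crossings at 0.02, the average log HR (truncated normal) corresponds to an HR of about 2.6 to 2.8, against a true 1.91.

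The second endpoint can only add to the chance of crossing.

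**4. Spending benchmarks at t = 49/130 = 0.377.** O'Brien-Fleming-type spending allows about 0.0005 to 0.0014 two-sided, depending on the form; Pocock-type allows about 0.025. The stated 0.02 is close to Pocock.

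**5. Error under no effect, if a crossing counts as a result.** Simulation of two correlated endpoints, interim-final correlation √t: interim at the stated threshold on either endpoint, then a final max-|z| test at 5% family-wise.

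| Endpoint correlation | 0 | 0.5 | 0.9 |
|---|---|---|---|
| False crossing at interim | 4.0% | 3.7% | 2.9% |
| Total two-sided error | 8.0% | 7.8% | 7.0% |
| False benefit (nominal 2.5%) | 4.0% | 3.9% | 3.5% |
| Total, benefit at 0.001, harm unchanged | 6.6% | 6.4% | 6.1% |
| Total, 0.001 in both directions | 5.1% | 5.1% | 5.1% |

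With benefit at 0.001, false benefit is about 2.5% at every correlation, whichever harm threshold is used.

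**6. Sensitivity.**

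- A single endpoint gives 6.3% in total.
- Stepdown-adjusting the interim p values to 0.02 overall gives 6.3 to 6.4%.
- Counting information against the 94 powered participants (49/94 = 0.521) gives 7.6% down to 6.7%.
- Keeping 0.02 per endpoint and holding 5% in total would need a final family-wise level of about 1.5 to 2.7%.

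**The case against.** **No consequence is attached to a crossing.** The section speaks of detection, the committee's role is advisory, and the Discussion disclaims using tests as decision rules, though there the subject is results that differ by measurement method or adjustment. If a crossing only prompts discussion and the trial runs to 130, the final analysis remains the confirmatory test and error stays near 5%. This stands: the inflation is conditional. Against it, a numerical threshold given to a committee that advises on recruitment has little function unless something may follow.

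**The final level may be reduced elsewhere.** A statistical analysis plan or committee charter, not shown, could do this or could bring the interim tests into the stepdown. This also stands. That no alpha is spent is an inference from silence and from the sample-size calculation. Keeping 0.02 would, however, require a final level well below the 5% used there.

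**The boundary is partly a matter of preference.** A Pocock-like level is a recognised choice when the final level is matched, and 'penicillin-like' has no numerical definition. That defends 0.02 as a group-sequential boundary, but not as a filter for a dramatic effect when an HR of 2.1 to 2.2 passes it and 1.91 is the plan.

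**Stronger readings a reader might infer.** One is that the article's 5% control has definitely failed; the two points above show why the text does not establish that. Another is that the benefit threshold alone produces 7 to 8%. It does not, because that figure includes false harm crossings.

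**Conclusion.** The mismatch between threshold and stated purpose holds whatever an unseen analysis plan says about alpha. It rests only on the article's planned effect, the 49 participants and an assumed 34 to 39 healing events.

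The error inflation holds under two conditions: that a crossing is acted on or reported as a positive finding, and that the final analysis stays at 5% family-wise. The part that matters for an efficacy claim is false benefit, a rise of about 1.0 to 1.5 percentage points. The larger two-sided total depends also on the assumed endpoint correlation and on whether the interim p values are stepdown-adjusted. No reading examined brings the total back to 5% while both conditions hold and 0.02 is kept.

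**What to change.** In Interim analyses {21b} and the committee's charter:

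1. For benefit, replace the threshold with two-sided p<0.001 (Haybittle-Peto), applied to one pre-named version of each main endpoint (measurement method and adjustment fixed). The final level need not change.
2. State what a crossing leads to, and that the final family-wise level remains 5%.
3. Decide the harm threshold openly. It may stay at 0.01 one-sided, since a false harm signal does not create a false efficacy claim. The text should then state that total two-sided error is about 6.0 to 6.6%, the excess being due to false harm signals only. The 5.1% total applies only if 0.001 is used in both directions.

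The cost is a few sentences and no extra participants. The real downside is a smaller chance of an early benefit signal on time to healing at the planned effect, down from 33 to 38% to 8 to 10%, which is what a search for a dramatic benefit implies.

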#### Activity measurement

All participants will be invited to wear a pedometer (Model: Mi Smart Band 5, Model: XMSH10HM) on the ankle of their non-affected limb (or non-index case affected limb) which they will wear from the first dressing change until 42 days (the point where cross-over may occur) or discharge, whichever comes first. This will act as a proxy measure of weight bearing and enable us to monitor activity across intervention and control groups and thereby evaluate whether the level of activity is similar across groups.

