#### Explanation for the choice of comparators {6b}

The comparator is usual care. Participants in the control group will receive usual care of twice-weekly standard saline dressings only and will not have blood taken. The clinical care of these participants will be identical to the intervention participants.

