#### Outcomes {12}

The main end-points will be:
‘Rate of healing’ based on two observations per week of ulcer size censored at 42 days (cm^2^ per unit time). We will estimate the effect of the intervention on the change in the ulcer size per unit time, i.e. the rate of healing (see Statistical Analysis).Time to complete re-epithelialization (right-censored at 42 days).

Both end-points will be analysed with and without adjustment for baseline characteristics (trial ulcer area and participants’ age), but we prefer unadjusted outcomes in randomised studies and therefore declare them as ‘primary’.

Secondary end-points:
Rate of healing based on two observations per week up to 70 days (cm^2^ per unit time) (calculated as described below).Time to complete re-epithelisation (observed up to 70 days).Generic quality of life (QoL) measured at first dressing change, fortnightly during in-patient stay and at 6-month follow-up, using the EQ-5D 3L. This scale has previously been used and validated in a Nepali population [17]. As far as we are aware, there is no valuation tariff in the Nepalese population, although this may change by the time that the analysis starts. Therefore, we propose not to prespecify the tariff but instead select the tariff at a later date. We note that tariffs are currently available for nearby countries including Sri Lanka [18] and China [19, 20].Longer-term outcomes measured at 6-month follow-up from randomisation will be proportion with:
i.Recurrence of treated ulcer;ii.Appearance of new ulcer;iii.Anatomical changes in the limb;Days hospitalised prior to discharge and total (to include any readmission due to leprosy/ulcers) by 6 months.Health economic information:
i.Number of visits to any healthcare facility from discharge to the end of follow-up at 6 months.ii.Data on the time taken to change dressings at the twice weekly changes.

Rate of healing will be assessed from blindly assessed photographs (Fig. 2). However, as complete healing may trigger discharge, we will monitor for cases discharged before the blinded assessor in Birmingham has noted complete re-epithelization.

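### The 70-day secondary endpoints run past the point where controls may cross over, and the complier analysis named for them does not recover the effect of L-PRF against saline only

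*Protocol article*

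**What the plan says.** Outcomes {12} ends both primary endpoints at day 42: ulcer size is "based on two observations per week of ulcer size censored at 42 days", and the other is "Time to complete re-epithelialization (right-censored at 42 days". The same section lists two secondary endpoints that run on: "Rate of healing based on two observations per week up to 70 days" and "Time to complete re-epithelisation (observed up to 70 days". It does not say that the comparator may change between days 42 and 70.

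Crossover appears elsewhere. Under Activity measurement the pedometer is worn "until 42 days (the point where cross-over may occur) or discharge, whichever comes first". Outcomes {12} and Plans for assessment {18a} say the same about step counts. Interim analyses {21b} sets a threshold of one control in ten crossing at day 42; above it, the remedy is given as "we will consider performing a complier average causal effects analysis to the 70 day outcome". No estimator is named.

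The Abstract and Aim and objectives {7} describe the control treatment as saline dressings only. Explanation for the choice of comparators {6b} goes further: "Participants in the control group will receive usual care of twice-weekly standard saline dressings only and will not have blood taken". Intervention description {11a} says that L-PRF is made from the participant's own blood and that dressing changes continue in both groups until healing or day 70. Missing data {20c} states analysis by intention to treat.

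**The concern.** A control who crosses to L-PRF must have blood taken, which {6b} rules out. The article therefore gives two accounts of what the control arm may receive after day 42, and the 70-day endpoints depend on which one applies.

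Dressings stop at healing, so the only controls still on dressings at day 42 are those who have not healed. If some of them then receive L-PRF, the 70-day intention-to-treat contrast is diluted relative to L-PRF against saline only. The named remedy divides the intention-to-treat difference by the share who did not cross. That is correct only if would-be crossers would do equally well in both arms (the exclusion restriction). Here their counterparts in the L-PRF arm have had 42 more days of L-PRF.

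At stake is the reading of both 70-day endpoints. A reader could take a diluted contrast, or a ratio that looks corrected, as the effect of L-PRF against saline.

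**Working it through.** **Inputs.** From Sample size {14}: 70% of controls and 90% of L-PRF participants healed by day 42, constant proportional hazards, two-sided 5%, 80% power, 1:1 allocation, 47 per group needed and 65 recruited. From Outcomes {12} and {21b}: crossover at day 42, endpoint at day 70. Assumptions of this check: crossers take on the L-PRF hazard from day 42, and the complier estimate is the usual ratio, intention-to-treat difference ÷ (1 − share crossing). The share crossing is not given, so a range is shown.

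**Reproducing the plan's figure.** HR = ln(0.10)/ln(0.30) = 1.912. Events (Schoenfeld) = 4 × (1.960 + 0.842)² / (ln 1.912)² ≈ 75. With a mean event probability of 0.80, 75/0.80 = 93.75, or 47 per group. This agrees with the article, so these hazards are the plan's own.

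**Day 70 without crossover.** Unhealed on L-PRF: 0.1^(70/42) = 0.0215. Unhealed on control: 0.3^(70/42) = 0.1344. Difference 0.1129, or 11.3 points.

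**Day 70 with crossover.** Let x be the share of all controls who cross; x is at most 0.30, the unhealed share. Control unhealed at day 70 = x × 0.1^(28/42) + (0.30 − x) × 0.3^(28/42) = 0.2154x + 0.4481(0.30 − x).

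| x | Control unhealed | ITT difference | Complier estimate | Complier ÷ no-crossover effect |
|---|---|---|---|---|
| 0.10 | 0.1112 | 0.090 | 0.0896/0.90 = 0.100 | 88% |
| 0.15 | 0.0995 | 0.078 | 0.0780/0.85 = 0.092 | 81% |
| 0.30 | 0.0646 | 0.043 | 0.0431/0.70 = 0.062 | 55% |

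Thirty per cent of 65 is about 20 controls. The 10% trigger is passed once more than a third of them cross (0.10/0.30).

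**Why the ratio misses.** Take x = 0.30. Those who do not cross are exactly the controls healed by day 42. If L-PRF would not delay their healing beyond day 70, their own day-70 effect is 0. The whole difference of 0.0431 then comes from the would-be crossers, whose healing differs between arms by 0.0431/0.30 = 0.144, where the method needs 0. The ratio of 0.062 equals neither the complier effect (0) nor the no-crossover effect (0.113).

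**Sensitivity.** A simulation with gamma frailty (variance 0.5, an assumption) gave a no-crossover effect of 0.130. Complier estimates were 0.104 to 0.107 at 15% crossing and 0.066 at 30%. Would-be crossers' day-70 healing differed between arms by 0.15 to 0.21.

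**Cox scale.** In a large simulation with true HR 1.91, the 70-day intention-to-treat HR was about 1.81 if half the unhealed controls cross and 1.72 if all do. The day-42 HR stayed at about 1.90.

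**The case against.** The design protects the main inference. Both primary endpoints stop where crossover may begin, the analysis is by intention to treat, and the complier analysis is only to be considered, above a threshold, for a secondary outcome. All of that stands, and a reader who inferred that the primary result is compromised would be wrong.

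The 70-day intention-to-treat comparison is also valid for a policy question: immediate L-PRF against saline with possible later L-PRF. To call it biased would go too far; it is diluted relative to L-PRF against saline only, and only if L-PRF works.

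The risk-difference scale makes the problem look larger than the planned Cox analysis would. ln(1.81)/ln(1.91) ≈ 92% and ln(1.72)/ln(1.91) ≈ 84%, so most of the log hazard ratio survives. At 10% crossing the complier estimate falls short by 11.3 − 10.0 = 1.3 points, while with 65 per arm the standard error of the no-crossover difference is √[(0.978 × 0.022 + 0.866 × 0.134)/65] ≈ 4.6 points. In every scenario computed, the complier estimate lies closer to the no-crossover value than intention to treat does. These points stand and limit the severity.

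The saline-only wording may describe allocated treatment, with crossover a departure from it. The full protocol or the figures not shown may also give a crossover criterion. That is possible, but the statement in {6b} about blood carries no such qualification.

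It could also be said that the choice of estimator belongs in the analysis plan. However, the article itself fixes the method, the trigger and the outcome, and the objection is to that stated choice.

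Two stronger readings are tempting. One is that controls cross because they have not healed; the article states no criterion, and only their eligibility to cross follows from {11a}. The other is that outcome-related crossover alone defeats a complier analysis. It does not, since such methods allow non-compliance related to prognosis. The failure lies in the exclusion restriction.

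**Conclusion.** The point holds for the two 70-day secondary endpoints. A standard complier average causal effect does not recover the effect of L-PRF against saline only: it gives 10.0, 9.2 and 6.2 points at 10%, 15% and 30% crossing, against 11.3 without crossover. The shortfall is modest near the trigger and large only if most unhealed controls cross.

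These sizes rest on the 70% and 90% assumptions, constant hazards, crossers taking on the L-PRF hazard, and the ratio form of the estimator. Since the article names no estimator, it cannot be said that every complier-type analysis must fail; one that models time-varying exposure could target the effect under its own assumptions.

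A reader might extend the point to hospital stay and the 6-month outcomes. Dilution there is plausible, but nothing in the documents allows it to be sized. The primary endpoints are not affected.

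**What to change.** 1. Reconcile the passages that describe controls as saline only, without blood taken, with those that provide for crossover at day 42, and state in the article who may cross.
2. Label the 70-day intention-to-treat results as a comparison of immediate L-PRF against saline with possible L-PRF from day 42.
3. Replace the complier analysis, as a supplementary analysis of time to healing, with a rank-preserving structural failure time model. State its assumption that L-PRF has the same relative effect whether started at day 0 or day 42.
4. Use inverse-probability-of-censoring weights only if enough unhealed controls do not cross. If half cross, about 10 remain (0.5 × 0.30 × 65); if all cross, none do and the weights cannot be formed.

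The model in item 3 does not cover the 70-day rate of healing, where the labelled intention-to-treat result would stand alone.

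The cost is wording and modest analysis work. Ulcer area is already measured twice weekly; the date of any crossover must be recorded. The downside is a wider interval and an untestable assumption that has to be stated.
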